
#### Safety assessment

Any AEs occurring throughout the complete study period, whether reported spontaneously by the participants or observed by the researchers, will be recorded and categorized as acupuncture-related AEs (e.g., fainting, broken needle, localized hematoma, dizziness), a side effect of TDG (e.g., skin irritation/itching, reddening, scaly skin), or a non-treatment–related AE. All AEs will be recorded in detail using a case report form.

#### Sample size calculation

This trial hypothesizes that 4 weeks of EA treatment will be superior to topical DSG in terms of pain relief in the dominant hand for patients with hand OA. Based on the results of a previous study [15], the OA pain intensity in the dominant hand on the 0–100 VAS scale was reduced by an average of 31.1 points in the topical DSG group and 23.9 points in the vehicle group. We predict that EA will display superiority over topical DSG by at least a 7-point better relative reduction in VAS score with a standard deviation of 12. Assuming a two-tailed test with a possible drop-out of 10% of the patients, a total of 108 patients (54 in the EA group and 54 in the topical DSG group) will be required for 80% power on a 5% alpha level.

#### Statistical analysis

The null hypothesis is that the change from baseline in the average overall finger joint pain intensity in the dominant hand at week 4 will be the same for the EA group and the topical DSG group. Data for continuous variables will be presented as means with standard deviations or medians with interquartile ranges, and for categorical variables, the data will be shown as frequencies (number of cases) and relative frequencies (percentages). For analysis of normally distributed quantitative variables, repeated-measures analysis of variance (ANOVA) will be used, while for the data of the groups with abnormal distribution, a nonparametrical Kruskal–Wallis test will be performed. Categorical variables will be analyzed using the Chi-square (*χ*^2^) test. Two-tailed *P* value < 0.05 is considered statistically significant. All outcome variables will be analyzed on an intention-to-treat (ITT) principle with an all randomized population included using SPSS software V.26.0 (IBM SPSS Statistics; IBM Corp, Somers, NY). We will impute missing primary outcome data by using multiple imputation techniques under the missing at random assumption for the ITT population, and we will not impute missing secondary outcome data.

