### Study setting and recruitment

This trial will be conducted at Guang’anmen Hospital, China Academy of Chinese Medical Sciences, and Yantai Hospital of Traditional Chinese Medicine from August 2020 to August 2022. A total of 108 participants will be publicly recruited through the use of posters and hospital websites. The duration of the trial for each participant will be 17 weeks: 1-week baseline, 4-week treatment, and 12-week follow-up.

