### Inclusion criteria

Age ≥ 18 years and ≤ 80 years;History of hand OA for at least 3 months before enrollment;Reported an average overall finger joint pain intensity in the dominant hand over the past 48 h of at least 40 mm according to a 100-mm visual analog scale (VAS, 0 = no pain, 100 = maximal pain). Patients applying NSAIDs at the screening must have an increase in pain in the dominant hand of ≥ 20 mm during washout;Posterior–anterior radiographs show Kellgren–Lawrence grade 1, 2, or 3 changes [24] in symptomatic joints;Tests for rheumatoid factor and anticyclonic citrullinated peptide are negative to exclude inflammatory arthritis;Ability to comply with the study protocol, understand the medical information form, and provide written informed consent.

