### Outcome measures

#### Primary outcome

The primary outcome in this trial is the change in average overall finger joint pain intensity in the dominant hand over the previous 48 h, measured on a 0–100 VAS (0 = no pain, 100 = maximal pain) from baseline to week 4. The changes at week 8 and week 16 from baseline also will be assessed.

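### The primary week-4 comparison uses change from baseline with no baseline covariate; adjusting for baseline VAS would be a near-free gain in precision of uncertain size

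*Protocol article*

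**What the plan says.** All references are to the protocol article.

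- **Primary outcome:** this section defines the endpoint thus: "The primary outcome in this trial is the change in average overall finger joint pain intensity in the dominant hand over the previous 48 h", from baseline to week 4 on a 0–100 VAS.
- **Statistical analysis, hypothesis:** "The null hypothesis is that the change from baseline in the average overall finger joint pain intensity in the dominant hand at week 4" is to be equal in the two arms.
- **Statistical analysis, method:** "For analysis of normally distributed quantitative variables, repeated-measures analysis of variance (ANOVA) will be used"; for other distributions "a nonparametrical Kruskal–Wallis test will be performed". No covariate is named for either. Missing primary outcome data are to be multiply imputed under missing at random.
- **Randomization and blinding:** all baseline measurements are finished before the envelope is opened. Allocation is in fixed blocks of 4, and no stratification is mentioned.
- **Inclusion criteria:** "Reported an average overall finger joint pain intensity in the dominant hand over the past 48 h of at least 40 mm".
- **Sample size calculation:** "at least a 7-point better relative reduction in VAS score with a standard deviation of 12", two-sided 5% level, 80% power, 10% drop-out, 54 per arm. No correlation with baseline enters the calculation.

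**The concern.** A difference in mean change uses baseline by subtracting it with a fixed weight of one. The weight that minimises the variance is the regression slope of week-4 VAS on baseline VAS, which in most pain data is below one. When the slope is below one, subtraction over-corrects: an arm that happens to start higher shows a larger fall for that reason alone, and this noise goes into the treatment comparison. Whether the repeated-measures ANOVA is run on changes or has baseline as a further time level, its week-4 group contrast is still the raw difference in change. Kruskal–Wallis does not adjust either.

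The precision at stake matters because the sample size has no slack: it is set to reach 80% power after the assumed drop-out.

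**Working it through.** **Inputs from the Sample size calculation:** difference 7; SD 12, read as the SD of the change because the assumed effect is a difference in reduction; two-sided alpha 0.05; power 80%; drop-out 10%.

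**Inputs not in the documents:** rho, the correlation of baseline with week-4 VAS; and k, the baseline SD divided by the week-4 SD. I show ranges for both.

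**1. Reproduce the plan's figure.** A two-sample t-test with standardised difference 7/12 = 0.583 needs 47.1, so 48 per arm. Then 48/0.9 = 53.3, so 54 per arm and 108 in total, exactly as stated. (The normal approximation gives 47 per arm, 53 after drop-out, 106 in total.) With 48 evaluable per arm the standard error is 12 × √(2/48) = 2.45, the noncentrality is 7/2.45 = 2.86, and the noncentral t with 94 df gives power of 80.7%.

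**2. Variance of ANCOVA relative to the change score.** Take the week-4 SD as 1 and the baseline SD as k.

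- Change score: k² + 1 − 2·rho·k
- Baseline-adjusted: 1 − rho²
- Ratio R = (1 − rho²)/(k² + 1 − 2·rho·k)

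The denominator equals (1 − rho²) + (k − rho)², so R never exceeds 1, and it equals 1 only when rho = k. With k = 1 it reduces to (1 + rho)/2.

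**3. Power with 48 per arm.** The residual SD is 12·√R; power is from the noncentral t with 93 df, one fewer for the slope.

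| k | rho | R | residual SD | power | worth in extra patients (1/R − 1) |
|---|---|---|---|---|---|
| 1 | 0.3 | 0.65 | 9.67 | 93.9% | 54% |
| 1 | 0.5 | 0.75 | 10.39 | 90.4% | 33% |
| 1 | 0.7 | 0.85 | 11.06 | 86.6% | 18% |
| 0.75 | 0.3 | 0.818 | 10.85 | 87.8% | 22% |
| 0.75 | 0.5 | 0.923 | 11.53 | 83.7% | 8% |
| 0.75 | 0.7 | 0.995 | 11.97 | 80.9% | 0.5% |
| any | = k | 1 | 12 | 80.7% | 0% |

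The rows with k = 0.75 are included because the 40 mm entry floor cuts off the lower part of the baseline distribution and not that of week 4, so a smaller baseline SD is plausible. In the last row the lost degree of freedom does not alter power at one decimal.

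**4. Size of a chance imbalance.** With k = 1 the SD at each visit is 12/√(2(1 − rho)): 10.1 at rho = 0.3 and 15.5 at rho = 0.7. One standard error of the baseline difference is that SD × √(2/48), which is 2.07 and 3.16 mm. It moves the difference in change by (1 − rho) times as much: 0.7 × 2.07 = 1.4 mm and 0.3 × 3.16 = 0.9 mm, against a target of 7 mm. ANCOVA removes this shift.

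**The case against.** **The article is silent and the SAP may adjust.** This is partly right. The article never calls the analysis unadjusted, model terms are often left to a SAP, and the hypothesis sentence alone would fit ANCOVA too, because modelling change or week-4 VAS with baseline as covariate gives the same treatment effect. But the article does more than state a hypothesis. It names the tests, and Kruskal–Wallis cannot take a covariate. The point is that a better method exists than the one named, not that detail is absent.

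**The design is sound as it stands.** This is correct. A reader might infer from the 40 mm floor that regression to the mean biases the comparison, that a chance baseline imbalance invalidates it, or that 108 patients are too few. The documents support none of these. Baseline is measured before allocation, so regression to the mean is expected equally in both arms, chance imbalance is random error already contained in the standard error, and the sample size reproduces exactly.

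**The gain may be small.** This stands. Quoting only the equal-SD figures would show the favourable part of the range; at k = 0.75 and rho = 0.7 the gain is 0.2 percentage points.

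**Hospital.** A reader might think a term for the two hospitals belongs with the main point. No stratification by hospital is stated, so the design does not call for one, and its gain cannot be computed from the documents. If hospital explained an assumed 1–5% of the variance of change, power would go from 81.5% to 81.9–83.4% (normal approximation).

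**Conclusion.** The point holds as a recommendation on efficiency. The planned test is valid and meets its own power target, and nothing here shows a bias or an error in the sample size. Adjusting for baseline VAS would lift power from 80.7% by anything from essentially nothing to about 13 percentage points (93.9 − 80.7 = 13.2) over the range tabulated. This rests on 12 being the SD of change, on a true difference of 7, on 48 evaluable patients per arm, and on assumed values of rho and k. The direction does not depend on rho or k: adjustment costs at most one degree of freedom. Baseline VAS carries the point; hospital is optional.

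**What to change.** For the primary outcome, replace both the repeated-measures ANOVA and the switch to Kruskal–Wallis with one prespecified model: ANCOVA of week-4 VAS on treatment and baseline VAS, or the week-4 treatment contrast of a mixed model with baseline VAS as covariate. Include baseline VAS in the multiple-imputation model. Treat the other continuous outcomes in the same way, each with its own baseline value. A hospital term may be added for one further degree of freedom, with probably little gain.

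The cost is a few sentences in the analysis section. The sample size, visits and data collection do not change. The change should be made before anyone sees outcome data by group, since a covariate chosen afterwards would look driven by the results.

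### The named analysis (repeated-measures ANOVA, or Kruskal–Wallis for non-normal data) is not tied to the week-4 null on which the trial was sized, and the test switches on the observed distribution

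*Protocol article*

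**What the plan says.** The Statistical analysis section of the protocol article opens by fixing the hypothesis: "The null hypothesis is that the change from baseline in the average overall finger joint pain intensity in the dominant hand at week 4" is equal in the two arms. The Primary outcome section agrees, with pain "measured on a 0–100 VAS (0 = no pain, 100 = maximal pain) from baseline to week 4". A separate sentence there adds two later visits: "The changes at week 8 and week 16 from baseline also will be assessed".

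The Sample size calculation assumes "at least a 7-point better relative reduction in VAS score with a standard deviation of 12", with 80% power, a two-sided 5% level and 10% drop-out, and arrives at 54 per group.

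For the analysis itself, the Statistical analysis section says "For analysis of normally distributed quantitative variables, repeated-measures analysis of variance (ANOVA) will be used". When normality fails, it changes to a Kruskal–Wallis test. These rules cover quantitative variables in general. The same paragraph prescribes multiple imputation for the primary outcome in all randomised participants. It does not say which visits enter the ANOVA, which of its terms answers the primary question, or to which visit the rank test applies.

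**The concern.** The hypothesis and the sample size concern one quantity: the between-group difference in VAS change at week 4. A repeated-measures ANOVA over the post-baseline visits reports two between-group results by default:

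- a group effect, which averages the visits;
- a group-by-time interaction, which asks whether the difference varies over visits.

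Neither is the week-4 difference. The planned treatment lasts 4 weeks in both arms, so weeks 8 and 16 fall after it, and the difference there need not equal that at week 4.

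Secondly, whether a parametric or a rank test is used depends on how the data turn out. The two branches target different quantities (means in one, ranks in the other), and the rank test by itself gives no difference in VAS points to set against the planned 7.

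At stake is the main conclusion. A real week-4 benefit could be missed, or a trial with no week-4 difference could be called positive, depending on which term is read.

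**Working it through.** **1. Reproduce the sample size.** Inputs from Sample size calculation: difference 7, SD 12, two-sided 5%, 80% power, 10% drop-out.

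- Normal approximation: n = 2 × (1.960 + 0.842)² × (12/7)² = 46.1, so 47 per arm. Then 47/0.9 = 52.2, so 53 per arm and 106 in total.
- Two-sample t-test (noncentral t): 47 per arm gives 79.9% power and 48 gives 80.7%, so 48 per arm. Then 48/0.9 = 53.3, so 54 per arm and **108 in total**, which matches the plan.

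The stated N and power are therefore those of a single two-group comparison of change.

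**2. What each test has as its null.** Let d4, d8 and d16 be the true differences in change at the three visits.

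- Week-4 comparison: d4 = 0.
- ANOVA group effect on the changes: (d4 + d8 + d16)/3 = 0.
- Group-by-time on the changes: d4 = d8 = d16.

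Only the first is the stated null.

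**3. Size of the mismatch.** Assumptions: 48 completers per arm, SD 12 at every visit, and equal correlation ρ between the changes. The document gives neither ρ nor the pattern of differences over time, so ρ = 0.5 and 0.7 and the profiles below are illustrative.

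- Week 4: SE = 12 × √(2/48) = 2.449; noncentrality 7/2.449 = 2.858; power 80.7%.
- Group effect: SE = 12 × √((1 + 2ρ)/3) × √(2/48), which is 2.000 at ρ = 0.5 and 2.191 at ρ = 0.7. For 7/3.5/0 the mean difference is 3.5, so the noncentrality is 1.750 or 1.598, and power 41% or 35%.
- Interaction: λ = (48/2) × Σ(dj − mean)² / (144 × (1 − ρ)), with F on 2 and 188 df. For 7/3.5/0 the sum is 3.5² + 0 + 3.5² = 24.5, so λ = 588/72 = 8.17 or 588/43.2 = 13.61, and power 72% or 92%.

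Rejection rates (ρ = 0.5 / ρ = 0.7). The last column is simulated, with 6,000 trials per scenario:

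| True differences, weeks 4/8/16 | Week-4 test | Group effect on changes | Group-by-time on changes | Group-by-time with baseline as a visit |
|---|---|---|---|---|
| 7 / 3.5 / 0 | 81% | 41% / 35% | 72% / 92% | 79% / 93% |
| 7 / 7 / 7 | 81% | 93% / 89% | 5% / 5% | 83% / 76% |
| 0 / 3.5 / 7 (week-4 null true) | 5% | 41% / 35% | 72% / 92% | 80% / 93% |
| 0 / 0 / 0 | 5% | 5% / 5% | 5% / 5% | 5% / 5% |

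Simulation of the two terms on the changes agrees to within about two percentage points. At ρ = 0.3 the group effect rejects 49% and the interaction 56% in rows 1 and 3.

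Rows 1 and 3 give the same rates for the two terms on the changes. Under these assumptions, those terms cannot tell a difference at week 4 that fades from one that is absent at week 4 and appears later.

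**4. The rank branch.** With two arms, Kruskal–Wallis is the Wilcoxon–Mann–Whitney test. Applied to the week-4 change under the same assumptions, it rejects about 5% under the null and has 78–80% power. It is valid for week 4 but compares ranks, and whether it is used depends on the data.

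**The case against.** The strongest reply is that the text does not commit to the omnibus reading. The paragraph opens with week 4, and weeks 8 and 16 are set apart in the Primary outcome section. An ANOVA with only baseline and week 4 has a group-by-time term identical to the t-test on change, which is the test that gives 108. A model over all visits can supply a week-4 contrast. Kruskal–Wallis on the week-4 change also addresses week 4, at close to the planned power. Choosing the term could be left to a statistical analysis plan that is not shown.

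All of this stands as far as it goes, and it rules out several stronger readings that a reader might infer:

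- **That the named methods cannot test week 4.** They can under some readings; the text does not select one.
- **That the sample size is wrong.** It reproduces exactly for a week-4 comparison.
- **That an ANOVA result cannot be pooled over imputations.** With two arms the group effect is a 1-df estimate with a standard error and pools by Rubin's rules, and pooling methods exist for multi-df tests.
- **That the error rates in the table are forecasts.** They depend on assumed profiles. If the difference persists at 7, the group effect does better than planned; if there is none at any visit, nothing is inflated.

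The reply does not remove the point. What the article does state is a test family and a switch on the observed distribution. An analysis plan that fixed one week-4 test regardless of distribution would have to depart from that statement. Until then, several analyses fit the text and can give opposite answers to the primary question.

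**Conclusion.** The concern holds in this form: the named analysis is not tied to the week-4 null, and the choice of primary test depends on the observed distribution. If the ANOVA is run over weeks 4, 8 and 16 and read through its omnibus terms, a 7-point week-4 difference that fades is detected by the group effect only 35–41% of the time, against about 81% for the direct test. A lasting 7-point difference is found by the interaction on the changes only about 5% of the time. With the week-4 null true and differences emerging later, the two terms reject in 35–41% and 72–92% of trials.

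These sizes rest on the assumed correlations and profiles. That the omnibus nulls differ from the week-4 null does not. Because the point governs the trial's main conclusion, it should be settled before the data are analysed.

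**What to change.** State that the primary analysis is the EA minus DSG difference in VAS change at week 4, with 95% CI. It should come from one pre-specified baseline-adjusted linear model, or from the week-4 contrast of a mixed model for repeated measures. Fit it in all randomised participants, pool the estimate over the imputations by Rubin's rules, and use it whatever the observed distribution. Make the week-8 and week-16 contrasts secondary, and keep a rank test on the week-4 change as a sensitivity analysis only.

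The cost is a few sentences in the Statistical analysis section, with no new data or visits. N stays 108: a direct week-4 comparison has 80.7% power with 48 completers per arm, and 85.2% if all 54 complete.

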**Methods:**

A total of 108 participants with hand OA according to the American College of Rheumatology criteria will be recruited and randomly assigned to the EA group or topical DSG group with a 1:1 allocation ratio. Participants in the EA group will receive EA treatment thrice weekly for 4 weeks, followed by a 12-week follow-up. In the topical DSG group, topical DSG at a dose of 2 g over the affected joints per hand will be applied four times per day for 4 weeks. The outcomes will be measured at weeks 4, 8, and 16. The primary outcome will be the change in average overall finger joint pain intensity in the dominant hand from baseline to week 4. All outcome variables will be analyzed on an intention-to-treat principle. All statistical tests will be two-sided.

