#### Secondary outcomes

The secondary outcomes are as follows:The proportion of participants achieving at least a 15-point reduction in average overall finger joint pain intensity in the dominant hand from baseline to weeks 4, 8, and 16: As previously described, 15 of 100 mm for absolute improvement could reflect a minimum clinically important improvement in pain for patients experiencing hand OA [27].Change in Australian Canadian Osteoarthritis Hand Index (AUSCAN) total score, and pain, stiffness, and physical function subscales from baseline to weeks 4, 8, and 16: The AUSCAN index contains a 15-item scale referring to hand pain (5 items), stiffness (1 item), and function (9 items) during the preceding 48 h [28], which is valid, reliable, and responsive in patients with hand OA [29]. All items are scaled on a 0–100 VAS (0 = none to 100 = very severe), with higher scores indicating more severe symptoms/functional impairment. The AUSCAN functional assessments will be performed for the dominant hand only. The total AUSCAN score will be calculated as the average of scores on 15 questions [29].Change in Functional Index for HOA (FIHOA) [30] from baseline to weeks 4, 8, and 16: The FIHOA is a patient-reported hand function questionnaire, comprising 10 items with a total score is calculated, ranging from 0–30 (0 = best activity performance, 30 = very poor activity performance).Change in the number of self-reported painful joints and painful joints at digital pressure and swollen joints from baseline to weeks 4, 8, and 16.Change in hand grip strength and pinch strength of the fingers from baseline to weeks 4, 8, and 16: Hand grip strength and pinch strength of the fingers of the dominant hand will be tested using a hand dynamometer (KYTO 2324, Kangdu Electronic Manufacture Co. Ltd, Dongguan, China) and a Jamar digital pinch gauge (Allegro Medical, Illinois, USA), respectively. Grip strength will be measured first, followed by pinch strength of the fingers, including palmar (three-jaw chuck) pinch, key (lateral) pinch, and tip (two-point) pinch [31]. For each of the tests, the participants will be in a standing position with the shoulder adducted and neutrally rotated and the elbow slightly extended [32]. Participants will conduct three trials, with an interval of 30 s at a minimum between each trial. The final score for analysis will be recorded in kilograms, and the average of the three consecutive values measured.Change in patient global assessment of improvement [33] from baseline to weeks 4, 8, and 16: The patients will be asked to respond to the question “Considering all the ways your hand OA affects you, how have you been during the last 48 h?” [34] on a self-administered 0–100 VAS (0, worst possible, to 100, best possible, in 10-point increments) at 4, 8, and 16 weeks.The proportion of responders according to the Outcome Measures in Rheumatological Clinical Trials (OMERACT) and Osteoarthritis Research Society International (OARSI) responder criteria [35] at weeks 4, 8, and 16: The OMERACT-OARSI response is defined as an improvement in either pain (0–100 overall finger joint pain) or function (0–100 AUSCAN physical function) by ≥ 50% (relative) and ≥ 20/100 (absolute); or an improvement of ≥ 20% (relative) and ≥ 10/100 (absolute) in ≥ 2 of the following: pain, functioning, and patient global assessment of improvement.Change in quality of life assessed by the World Health Organization Quality of Life abbreviated version (WHOQOL-BREF) from baseline to weeks 4, 8, and 16: The WHOQOL-BREF is a 26-item self-report questionnaire rated on a 5-point Likert-type scale with four domains of QOL: physical (7 items), psychological (6 items), social (3 items), and environment (8 items), plus two items representing the general QOL [36]. The four domain scores are scaled in a positive direction with higher scores indicating a higher QOL. In this trial, we will use the Chinese version of the WHOQOL-BREF, which has been reported to have adequate reliability and validity [37].Participants’ expectations for acupuncture at baseline: At baseline, participants in the EA group will be asked to answer the following question: “What level of improvement do you expect from EA for your hand OA?” Participants can choose one of the following five answers: “extreme improvement,” “moderate improvement,” “slight improvement,” “no improvement,” or “unclear.”Self-reported consumption of acetaminophen for hand OA during weeks 1–4 and weeks 5–12: the proportion of participants using acetaminophen and the average dosage of acetaminophen used weekly will be calculated and assessed.

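### Secondary outcomes are promised an analysis of all randomised participants, but without imputation the named tests cannot deliver it

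*Protocol article*

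**What the plan says.** All the relevant statements are current text of the protocol article.

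- **Population** (Statistical analysis): "All outcome variables will be analyzed on an intention-to-treat (ITT) principle with an all randomized population included". The abstract repeats the intention-to-treat promise for all outcome variables.
- **Missing primary data** (same section, next sentence): "We will impute missing primary outcome data by using multiple imputation techniques under the missing at random assumption for the ITT population".
- **Missing secondary data** (same sentence): "and we will not impute missing secondary outcome data".
- **Tests** (same section): "For analysis of normally distributed quantitative variables, repeated-measures analysis of variance (ANOVA) will be used"; for data that are not normally distributed, "a nonparametrical Kruskal–Wallis test will be performed"; and "Categorical variables will be analyzed using the Chi-square" test.
- **Visits** (abstract, Methods): "The outcomes will be measured at weeks 4, 8, and 16".
- **A secondary outcome built on the primary measure** (Secondary outcomes): "The proportion of participants achieving at least a 15-point reduction in average overall finger joint pain intensity in the dominant hand", at each of the three visits. The OMERACT-OARSI response in the same section also uses this pain score, together with AUSCAN function and the patient global assessment.

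The article names no mixed model, no non-responder rule and no other method that would keep a participant with a missing secondary value in the analysis.

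**The concern.** The population statement and the missing-data rule conflict for secondary outcomes. A test that needs an observed value, applied to data that are not imputed, covers only those observed. The primary and secondary results would then describe different sets of people under one intention-to-treat label.

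The clearest case is week 4. The primary outcome is the mean change in the pain VAS, and the 15-point responder rate is a cut of that same change at that same visit. A participant with a missing week-4 score would count in the mean and not in the responder rate. If the two summaries then disagreed, a reader could not tell whether the cause was the shape of the distribution or the difference in population.

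**Working it through.** **1. The plan's own figure.** Sample size calculation gives a 7-point difference, SD 12, 80% power, two-sided 5% and 10% drop-out. With a standardised difference of 7/12 = 0.583, a two-sample t-test needs 47.1, so 48 per group. Then 48/(1 − 0.10) = 53.3, so 54 per group and 108 in total. The stated 108 is reproduced. It is not in dispute and only sets the scale of the expected missing data.

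**2. What each named test does with a missing value that is not imputed.**

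| Test | Who is lost |
|---|---|
| Conventional repeated-measures ANOVA | Anyone missing any visit, from every visit's comparison |
| Kruskal–Wallis | Those missing at the visit tested |
| Chi-square | Those missing at the visit tested |

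Under the ANOVA, a participant who misses only week 16 also leaves the week-4 comparison. Under the other two tests that participant stays in at week 4. In neither case are all randomised participants included.

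**3. Size at the planned drop-out.** The 10% is a total for the trial.

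- Missing: 108 × 0.10 = 10.8, about 11, or 5 to 6 per arm.
- Remaining: 108 − 10.8 = 97.2, about 97.

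If drop-out is permanent, the ANOVA loses all of these participants at every visit. The visit-by-visit tests lose at most this number, and fewer at the earlier visits if some people leave late. Hence up to about 11.

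**4. Range for other total drop-out rates (assumed, not from the protocol).**

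- 5%: 108 × 0.05 = 5.4, about 5 absent and 103 left.
- 20%: 108 × 0.20 = 21.6, about 22 absent and 86 left.

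**5. Week-4 pain score under the two rules.**

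| Summary at week 4 | Status | Missing score is |
|---|---|---|
| Mean change in VAS | Primary | Multiply imputed |
| At least 15-point reduction in the same VAS | Secondary | Left missing |
| OMERACT-OARSI response, pain component | Secondary | Left missing |

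**The case against.** **Leaving secondary outcomes unimputed is a common choice, and the rule is stated openly beside the population claim.** This is true. Intention-to-treat in the sense of analysing people in the arm to which they were randomised is compatible with it. What is not compatible is the further clause that the whole randomised population is included for all outcomes. That clause is the fault.

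**An article condenses, and a SAP may settle this.** The article does not leave the matter open. It fixes the population, the tests and the missing-data rule itself, and these conflict as written.

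**Larger losses.** A reader might infer that listwise deletion would leave only 79 or 93 of 108. Those figures are 108 × 0.9³ = 78.7 and 108 × 0.95³ = 92.6. They assume that 10% or 5% are missing independently at each of three visits. The protocol's 10% is a trial total, and with permanent drop-out about 97 remain. The ANOVA loses more only if visits are also missed intermittently, about which the document gives no figure. Nor are all secondary results restricted to participants complete at every visit, since that applies to the ANOVA alone.

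**Biased treatment comparison.** A reader might also infer that the observed-case rates would favour the arm losing more poor responders. One can construct this. With 3 EA and 8 gel drop-outs and 36 responders per arm, the observed rates are 36/51 = 70.6% and 36/46 = 78.3%, against 36/54 = 66.7% in both arms when all drop-outs count as non-responders. But the split is invented, and every drop-out is assumed to have failed. The Discussion acknowledges unblinded participants and possible poor compliance with the gel. It does not predict unequal loss to follow-up. The harm in this example is also not-at-random loss, which missing-at-random methods would not remove. It therefore does not measure the present problem.

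**Conclusion.** The point holds as a contradiction between a promised population and the methods given to deliver it, confined to secondary outcomes. At the planned 10% total drop-out, up to about 11 of 108 participants (5 to 6 per arm) would be in the primary analysis through imputation and absent from secondary analyses. This assumes that those who drop out also lack the secondary measurements. The week-4 pain score would be handled in two different ways for two summaries of one measurement.

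The primary analysis, its imputation and the sample size are unaffected. The documents do not show that treatment comparisons on secondary outcomes would be biased, or in which direction. The change is worth making before analysis because it is cheap and because the current wording would label results as covering all randomised participants when they do not.

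**What to change.** 1. Analyse continuous secondary outcomes with a likelihood-based mixed model for repeated measures using every observed visit. This rests on the same missing-at-random assumption as the primary and avoids dropping a participant from all visits for missing one. A participant with no post-baseline value still adds little or nothing, so describe the analysed set accordingly.
2. Derive the 15-point responder from the multiply imputed VAS data, so that at week 4 it rests on the same participants as the primary. For weeks 8 and 16, state that the imputation covers those visits too.
3. For OMERACT-OARSI response, state a rule for missing components or missing response, or label the analysis observed-case.
4. Remove the all-randomised claim from any secondary analysis that stays observed-case. This wording change alone would resolve the contradiction; items 1 and 2 also bring the analysed set into line with the primary.
5. Optionally, add a sensitivity analysis that counts missing responders as non-responders, since items 1 and 2 do not protect against drop-out that is not at random.

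The cost is revised analysis wording and modest extra programming. No new data and no change to sample size are needed.
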